## Abstract

**Background:**

Cancer is a medical condition where some cells of the body reproduce uncontrollably and metastasize to other parts of the body. The burden of the disease is significantly high both at the global and national levels. In UAE, cancer was found to be the third leading cause of death. Breast cancer has been ranked first due to its prevalence, incidence, and mortality in UAE. Breast cancer survivors have significantly poor cardiovascular tolerance which affects their quality of life (QoL), even after the carcinoma has been treated or removed. Thus, the protocol aims to analyze the changes in cardiovascular endurance and QoL domains for breast cancer survivors in the United Arab Emirates using a long-term 2-month physical rehabilitation.

**Methods:**

A total of 60 breast cancer survivors would be included in the study using a randomized controlled allocation of a 2-month physical rehabilitation intervention program with 3 months of follow-up. The intervention would target the cardiovascular endurance component of the participants to improve their physical well-being and quality of life ultimately.

**Discussion:**

The findings of the study would have high clinical significance among breast cancer survivors in the UAE. The proposed physical rehabilitation program could be beneficial in improving cardiovascular endurance and thereby reduce the risk of mortality among breast cancer survivors. In addition, the physiological benefits of the exercise program could improve their quality-of-life domains including physical, mental, and social well-being. On a larger view, it could also help to reduce the economic burden on the health system due to associated complications.

**Trial registration:**

ClinicalTrials.gov NCT06013527. Registered on 28 August 2023.

## Introduction

### Background and Rational {6a}

Cancer is a medical condition where some cells of the body reproduce uncontrollably and metastasize to other parts of the body [1]. The burden of the disease is significantly high both at the global and national levels. In the year 2020, 19.3 million total new cases of cancer were recorded, and cancer deaths were estimated to be 10.0 million, for both males and females. Out of this, Asia accounts for 58.3% of cancer deaths, while Europe constitutes about a quarter of total cancer deaths, estimated at 19.7%, and America has 14.2% cancer-related mortality [2]. In 2022, 2.3 million women were diagnosed with breast cancer, hence being the most common cancer in women in 157 countries out of 185 [2]. In UAE, cancer was found to be the third leading cause of death where breast cancer accounts for 21.4% [3]. Therefore, breast cancer was ranked first due to its prevalence, incidence, and mortality [3, 4]. The high burden of the disease prompts the medical community to explore and advance treatment options. This effort is seen in the decrease in the overall mortality rate by 40% from 1998 to 2012 [5]. However, breast cancer survivors have significantly poor cardiovascular tolerance which affects their quality of life (QoL), even after the carcinoma has been treated or removed.

Poor cardiovascular endurance has been very commonly reported among breast cancer survivors [6]. The cardiorespiratory system executes the main function of our circulatory system and provides energy for body movements. Poor functioning and endurance directly affect the individuals’ level of independence and ability to participate in the physical, mental, and social environment affecting the overall QoL. Furthermore, it is well known that QoL domains are interrelated where physical rehabilitation is of utmost importance as it can help to address all domains. In addition, physical rehabilitation forms an important part of breast cancer management pre- and post-surgical. In the pre-surgical phase, rehabilitation can help the individual to sustain the ill effect of post-surgical complications better. However, it is the post-surgical phase that requires more attention and rehabilitation strategies to combat the situation and help the individual regain their functional level near normal.

The importance and benefits of physical rehabilitation among breast cancer survivors have been well reported with evidence in the literature [7]. Studies report that physical rehabilitation techniques and exercise regimens can help to reduce pain, fatigue, weakness, and lymphedema and thus improve QoL [8]. Integrated structured exercise programs have been defined and prescribed to check their benefits over the QoL domains [9–11]. In addition, a study reported that while structured exercise programs should focus on improving cardiorespiratory fitness and muscular strength during exercise training, these programs should consider physical activity outside of training, if well-tolerated, to potentially further lower fatigue and improve QoL in cancer survivors [12]. Thus, an individual-centric approach could be more beneficial to match individual needs efficiently.

Although a recent study reported a higher incidence and prevalence of breast cancer in the UAE population [4], no published data was found on the application of evidence-based exercise regimens, rehabilitation programs, and guidelines for breast cancer survivors in the UAE. Therefore, the proposed research project aims to improve cardiovascular endurance in the QoL domains among breast cancer survivors in the United Arab Emirates using physical rehabilitation and recommended exercise programs.

### Objective {7}

The objective is to analyze the changes in cardiovascular endurance and QoL domains for breast cancer survivors in the United Arab Emirates using a structured physical rehabilitation program for 2 months with a follow-up after 3 months.

### Trial design {8}

Prospective, parallel-group, controlled, equal allocation ratio, randomized controlled trial of breast cancer survivors (hospitalized or homecare).

### Eligibility criteria {10}

During the screening and study period, the investigators will assess the patients for eligibility and collect demographic and medical history. The inclusion criteria are as follows:Breast cancer survivors who have undergone chemotherapy, mastectomy, and cleared for post-surgical physical rehabilitation.Age group 18 years to 65 yearsFemale participants (breast cancer survivors)Diagnosed with stage I to stage IIIa breast cancer. (As other stages of cancer include metastasis)The exclusion criteria are as follows:Patients diagnosed with prior cardiorespiratory disorders, cognitive dysfunction,and other health problems that would prevent safe participationActive breast cancer patientsParticipants who engaged in physical activity like the intervention group in any form

### Additional consent provisions for collection and use of participant data and biological specimens {26b}

Not applicable; the study does not use any biological specimens or provisions for additional data.

### Explanation for the choice of comparators {6b}

The comparators used in the study were chosen based on the study design and research question and to match the objectives of the study.

### Interventions {11a}

The intervention group will receive a structured exercise adapted from the BReast cancer and EXercise (BREX) program which has shown significant improvement in Quality of Life and Physical Fitness among breast cancer survivors [15]. The exercise program will continue for 2 months, and a follow-up will be done after 3 months. The exercise program is detailed in Table 1. Exercise would be prescribed and supervised by the physical therapist (FR and WA). The control group will continue with their routine life and will receive standard care given by the hospital.

**Table 1 Tab1:** Description of the proposed physical rehabilitation program among breast cancer survivors

Components of physical rehabilitation program Supervised—2 times a week Individually tailored program—3 times a week	Frequency (5 times a week for 2 months)
Supervised Training: Two types over alternate weeks: 1) 60-min step aerobics class 2) 60-min circuit training class Each class will include warm-up and cool-down periods both lasting 10–15 min. The maximum target rate of perceived exertion (RPE) would be set at 14–16 on a 20-point Borg scale, a level of exercise that feels “somewhat hard” or “hard” and coincides with about 86–92% of maximal heart rate, 76–85% of maximal VO_2_, and 5–7 metabolic equivalents (METs) ideal for improving the related domains of QoL and cardiovascular endurance [16]. During the first 3 weeks, the participants would exercise at a lower level of RPE (approximately 11–13), to adapt to the training	Twice a week
Unsupervised home program: Home training would consist of endurance training such as walking, Nordic walking, or aerobic training, but it would also include jumps and leaps like step aerobics (96 jumps and leaps per home training session) to promote bone health [15]. Warm-up and cool-down exercises, such as marching or climbing upstairs would be recommended before and after the home training session. Home training would be aimed so that the total training would comprise a minimum of five training sessions per week	Three times a week

### Strategy for Treatment modification and adherence {11b}{11c}

Participants will be removed if there is a change in the medical condition, if there are adverse effects noted, or if they choose to drop out. As the intervention is individually tailored, the required modification will be made depending on the patient’s physical ability to adapt to the given exercise protocol. The home program would be randomly and frequently monitored over audio or video phone calls along with a daily logbook which would be maintained and entered by the therapist after discussion with the patient.

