### Concomitant care {11d}

No participant will be restricted from receiving external care, if any participant in the intervention or control group is matching with the exercise program of the intervention group, the data would be excluded for statistical analysis.

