#### Data analysis {20a} {20b} {20c} {21b}

The data would be analyzed using the SPSS software package version 29. Descriptive and inferential statistics will be done to test the desired hypothesis. Paired and unpaired *t*-tests would be conducted to analyze the changes in the primary outcomes for within and between group analysis. Repeated measures of ANOVA would be done to determine the changes at baseline, end of intervention, and follow-up for the intervention group. If the trial needs to be terminated due to any reasons, interim analysis would be done for the average period of the trial for all participants and the trial would be terminated on a decision from the senior researchers (AH and PK). No adjusted analysis is planned for this research. Missing data would be analyzed through intention-to-treat analysis.

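### Excluding randomised participants' data for outside exercise contradicts the stated intention-to-treat analysis, and the removal rule for adverse effects is left unreconciled with it

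*Protocol article*

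**What the plan says.** Three sections of the protocol article bear on who is analysed.

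- **Concomitant care {11d}.** Participants may receive external care. If someone in the intervention or the control group is found to match the intervention's exercise programme, "the data would be excluded for statistical analysis".
- **Strategy for Treatment modification and adherence {11b}{11c}.** The removal rule reads "Participants will be removed if there is a change in the medical condition, if there are adverse effects noted"; choosing to drop out is the third reason in the same sentence. The next sentence treats adaptation separately: "the required modification will be made depending on the patient’s physical ability to adapt to the given exercise protocol".
- **Data analysis {20a} {20b} {20c} {21b}.** "Missing data would be analyzed through intention-to-treat analysis". This is the only mention of intention-to-treat. The tests are these: "Paired and unpaired *t*-tests would be conducted to analyze the changes in the primary outcomes for within and between group analysis". Repeated measures ANOVA follows, for the intervention group only, and "No adjusted analysis is planned for this research".

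On the comparator, Interventions {11a} says "The control group will continue with their routine life and will receive standard care given by the hospital".

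**The concern.** Intention-to-treat fixes two things: every randomised participant is analysed, and she is analysed in the arm she was allocated to. A rule that drops data because of what a woman did after randomisation breaks the first of these. Women who take up exercise on their own are unlikely to be a random subset, so the remaining groups are no longer the groups that randomisation formed.

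The removal rule raises a second, less certain problem. An adverse effect or a changed medical condition arises after randomisation and may well be related to fitness and quality of life. If removal ends outcome collection, these women have no 2-month or 5-month value. Intention-to-treat is not a method for missing data, so the sentence that assigns it that task leaves the gap open. At stake is whether the comparison on VO2 max and quality of life is between the randomised groups or between selected parts of them.

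**Working it through.** **1. The sections side by side**

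| Section | Trigger | Arms covered | Stated consequence | Compatible with intention-to-treat? |
|---|---|---|---|---|
| Concomitant care | Outside exercise matching the programme | Both | Data left out of the analysis | No |
| Treatment modification and adherence | Adverse effect, changed condition, own choice | Not limited to one arm | Removed, from what is not said | Only if outcomes are still collected and analysed |
| Data analysis | Missing data | Not stated | Handled by intention-to-treat | Names a principle, not a method |

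The first and third rows cannot both be followed. The second can be reconciled with the third, but the text does not do so.

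**2. What the planned tests do with a missing outcome**

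A t-test uses only observed values. Repeated measures ANOVA in its usual form needs all three time points. With no adjusted analysis, nothing else in the plan brings back a woman who has no outcome.

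**3. Inputs for size**

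From Sample size {14}: SD 5.9, target difference 3, 36 per group, 20% allowed for dropout and loss. The plan's own figure reproduces: 2 × (1.96 + 0.84)² × 5.9² / 3² = 60.65, printed as 60.6. Only the SD, the difference and the arm size are used below.

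Not in the documents, and therefore assumed: the number removed (m), how far their mean would have lain below the arm mean (the deficit), and that removal occurs in the exercise arm only.

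**4. Shift in the exercise-arm mean**

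With p = m/36, shift = p × deficit / (1 − p) = m × deficit / (36 − m).

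| m | Deficit | Calculation | Shift | Share of 3 |
|---|---|---|---|---|
| any | 0 | – | 0 | 0% |
| 2 | 3 | 2 × 3 / 34 | 0.18 | 6% |
| 4 | 5.9 | 4 × 5.9 / 32 | 0.74 | 25% |
| 6 | 5.9 | 6 × 5.9 / 30 | 1.18 | 39% |

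**5. Cross-check with a different model**

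Suppose a fraction d of the exercise arm is removed for low tolerance, and tolerance correlates with VO2 max at ρ. Then bias = ρ × 5.9 × φ(q) / (1 − d), where q is the d-quantile of the standard normal and φ its density.

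- d = 10%: 0.35 (ρ = 0.3) to 0.58 (ρ = 0.5).
- d = 20%: φ(q) / (1 − d) = 0.280 / 0.8 = 0.35, so 0.3 × 5.9 × 0.35 = 0.62 and 0.5 × 5.9 × 0.35 = 1.03, or 21% to 34% of the target. The standard error is 5.9 × √(1/28.8 + 1/36) = 1.475. With no true effect, the two-sided type I error rises from 5% to about 7% to 11%.
- ρ = 0: no bias at any d.

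Under this model, the case of 4 removed at a deficit of one SD needs ρ of about 0.59, so it lies toward the strong end.

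**6. The outside-exercise exclusion**

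The formula in step 4 applies to either arm. Leaving out fitter-than-average controls lowers the control mean and enlarges the difference; leaving out fitter-than-average women in the exercise arm shrinks it. The protocol gives no basis for the numbers in either arm, so neither the net direction nor the size can be stated.

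**The case against.** The strongest reply concerns the removal rule. It stands under a heading on treatment modification and adherence, its neighbouring sentences deal with adapting and monitoring the exercise, and Follow-up {18b} speaks of following up all participants in the intervention group. Removal could therefore mean no more than stopping the exercise. This reply partly stands. Set against it, the subject of the sentence is the participant, removal is listed beside dropping out, and adaptation has its own sentence, so leaving the study is the more natural reading. But nothing says that outcome collection ends.

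Three stronger readings are therefore tempting but not supported:

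- *That the removal rule itself contradicts intention-to-treat and is certain to bias the result.* The text leaves this open. The bias is conditional, and zero if outcomes are still collected and analysed or if removal is unrelated to outcome. Adapting the exercise to ability should also reduce removals.
- *That women who tolerated exercise would be compared with nearly all controls.* A changed condition and dropping out can occur in either arm, the outside-exercise exclusion covers both, and the 20% loss allowance is not limited to one. Only the concentration of exercise-related adverse effects in the exercise arm is a fair inference.
- *That removal hides harm.* Follow-up {18b} and Adverse event reporting {22} {30} provide for recording and reporting adverse effects.

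It can also be said that a condensed article may leave the missing-data method to an analysis plan. That is accepted: the absence of a named method is not the point. The point is that the article names something that is not a method. None of these replies touches the outside-exercise exclusion, which is explicit.

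**Conclusion.** The point holds in two parts of different strength. The exclusion under Concomitant care contradicts intention-to-treat as written, and following it gives a selected comparison whose direction the documents do not settle. The removal rule is an unreconciled conflict: if it ends outcome collection, the planned tests analyse completers and would tend to favour exercise.

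The size of the second part is an illustration, not an estimate. It rests on removal in the exercise arm only and on assumed numbers and deficits, and it runs from nothing to about two fifths of the target difference.

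**What to change.** Reconcile the three sections.

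1. In Treatment modification and adherence, leave the clinical rule for stopping exercise to the investigators, but state that stopping exercise is not leaving the study. Every randomised woman is assessed at 2 and 5 months unless she withdraws consent.
2. In Data analysis, state that each woman is analysed in her randomised arm. Replace the sentence on missing data with an actual method, such as a mixed model for the repeated outcomes.
3. In Concomitant care, take the exclusion out of the main analysis. Record outside exercise in both arms and use the exclusion only in a sensitivity analysis.

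The cost is wording in three sections, a few extra assessments, and possibly a smaller effect estimate. It should be done before outcomes are lost, because values that were not collected cannot be recovered at the analysis.

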### Concomitant care {11d}

No participant will be restricted from receiving external care, if any participant in the intervention or control group is matching with the exercise program of the intervention group, the data would be excluded for statistical analysis.

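### Excluding randomised participants because of the exercise they did conflicts with intention-to-treat and can bias the comparison, in a direction the article does not determine

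*Protocol article*

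**What the plan says.** Concomitant care {11d} opens by stating that "No participant will be restricted from receiving external care". The same sentence then sets a rule for the analysis: "if any participant in the intervention or control group is matching with the exercise program of the intervention group, the data would be excluded" from the statistical analysis. It names both arms and gives no threshold for what counts as matching.

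Data analysis {20a}-{20c} states that "Missing data would be analyzed through intention-to-treat analysis", and that "No adjusted analysis is planned for this research". The between-group comparison is an unpaired t-test. The section does not define an analysis population.

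Eligibility criteria {10} separately exclude people who already engage in activity similar to the programme. The rule in {11d} goes further, because it applies to people who have already been allocated and takes effect at analysis.

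**The concern.** Randomisation makes the two groups comparable only if the people analysed are the people randomised, or if any losses are unrelated to outcome. Here the losses are chosen by the plan, and they depend on exercise behaviour. In a trial sized on VO2 max, that behaviour is plausibly linked to the outcome in two ways: fitter people may be more likely to exercise, and exercise may raise fitness. With no adjusted analysis planned, nothing would offset the selection.

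The plan also cannot be followed consistently. An analysis run on intention-to-treat lines does not discard observed outcomes because of what a participant did after allocation, and {11d} requires exactly that. The rule decides who enters the primary comparison, so the estimate, its type I error and its precision are all at stake.

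**Working it through.** The article states no figure for this rule, so there is none to reproduce. The scale comes from Sample size {14}: SD 5.9, target difference 3, 36 per group. The formula there reproduces: 2 × (1.96 + 0.84)² × 5.9² / 3² = 545.82 / 9 = 60.65, against the stated 60.6. That result does not bear on the present point.

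The exclusion shares, the fitness gap and the correlations below are assumptions.

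**1. Simple shift in the control mean.** Let a fraction p of controls be excluded, and let them average δ above the other controls, whose mean is m. The full control mean is m + pδ, and after exclusion it is m. The shift is pδ.
- p = 0.10, δ = 3: 0.3 units; 0.10 × 36 = 3.6, about 4 controls lost.
- p = 0.20, δ = 3: 0.6 units; 0.20 × 36 = 7.2, about 7 controls lost.

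Against the 3-unit target this is 10-20%. The formula does not say why the excluded controls are higher.

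**2. Selection alone, no true effect.** Suppose the tendency to exercise has correlation ρ with outcome and the top fraction p is removed from one arm. The mean of those who remain falls by ρ × 5.9 × φ(z) / (1 − p), where z is the upper-p normal point and φ is the normal density.
- p = 0.10: φ(1.282) = 0.1755, so 5.9 × 0.1755 / 0.9 = 1.15. This gives 0.35 at ρ = 0.3 and 0.57 at ρ = 0.5.
- p = 0.20: φ(0.842) = 0.280, so 5.9 × 0.280 / 0.8 = 2.065. This gives 0.62 at ρ = 0.3 and 1.03 at ρ = 0.5.

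Simulation agrees. With 36 per arm and a nominal two-sided 5% test, at ρ = 0.3 and ρ = 0.5 respectively:

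| Excluded | Bias (VO2 units) | Type I error |
|---|---|---|
| 20% of controls only | +0.6; +1.0 | about 7%; 10% |
| 20% of both arms, equal selection | about 0 | about 5% |
| 20% of intervention arm only | −0.6; −1.0 | about 7%; 11% |

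**3. True effect of 3, and exercising controls gain it too.** With 20% of controls exercising, analysing everyone gives 3 − 0.20 × 3 = 2.4.
- Excluding those controls gives 3.0 with no selection (ρ = 0), 3.6 at ρ = 0.3 and 4.0 at ρ = 0.5.
- Excluding 20% of both arms with equal selection gives 3.0.
- Excluding 20% of the intervention arm only, with no control exercising, gives 2.4 (ρ = 0.3) or 2.0 (ρ = 0.5), where analysing everyone gives 3.0.

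**4. Literal reading.** Suppose 50-70% of the intervention arm adhere, gain 3 units and are excluded for matching, with no controls excluded. Analysing everyone gives 0.5 × 3 = 1.5 to 0.7 × 3 = 2.1. After exclusion the difference is about 0 at ρ = 0, and −1.4 to −2.1 at ρ = 0.3.

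**5. Precision.** By normal approximation and before dropout, power for a 3-unit difference is Φ(3 / (5.9 × √(1/36 + 1/36)) − 1.96) = Φ(0.20), about 58%. With 29 controls it is Φ(3 / (5.9 × √(1/36 + 1/29)) − 1.96) = Φ(0.08), about 53%.

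**The case against.** **Context and overlap with eligibility.** The sentence sits under concomitant care and follows a statement about external care, so the sensible reading is similar exercise obtained outside the trial, not the assigned programme. Eligibility already screens out people who do similar activity. The programme amounts to five sessions a week, so few controls may reach it. This has force: the literal reading is probably unintended, and the exclusion rate could be small. But home training includes walking and no threshold is given, so the rate could also be larger. On the sensible reading the exclusion still depends on behaviour after allocation.

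**Intention-to-treat is named only for missing data.** True, and an analysis population may be defined in a document not shown. The conflict is therefore partly implied. The exclusion itself is an explicit rule, however, and not a detail left for later.

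**Stronger readings the article does not support.**
- A reader might infer that the rule biases the result towards benefit. That follows only if exclusions fall mainly on exercising controls. The rule names both arms, and steps 2 to 4 show the sign can be positive, nil or negative.
- A reader might call the whole 0.3-0.6 shift spurious. If exercising controls are higher because they exercised, removing them takes out contamination. Only the part due to pre-existing fitness is false effect, and step 1 cannot separate the two.
- A reader might infer that matching is judged differently in the two arms, because adherence section {11c} describes a "daily logbook which would be maintained and entered by the therapist after discussion with the patient". That logbook monitors the home programme, and nothing ties it to this rule. The article does not say how matching is assessed in either arm.

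**Conclusion.** The rule is wrong as written. It excludes randomised participants, in either arm, by exercise done after allocation. That breaks the randomised comparison and cannot be reconciled with the intention-to-treat approach named under Data analysis. This conclusion rests on the text alone.

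Direction and size are not settled by the article. On assumed exclusion of up to 20% in one arm and correlations of 0.3-0.5, selection alone moves the difference by roughly 0.3 to 1.0 units either way, against a 3-unit target. Type I error at 20% exclusion is about 7-11%. Equal exclusion and selection in both arms gives about no bias when there is no effect. These figures are illustrations and not estimates for this trial. The change should be made before analysis because the rule decides who is in the primary comparison, and an unpredictable sign does not make the result easier to interpret.

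**What to change.** - In {11d}, delete the exclusion from the analysis. The statement on external care is unaffected.
- In {20c}, state that all randomised participants are analysed in their allocated group, whatever exercise they did.
- Record exercise outside the trial with the same question in both arms at each assessment.
- Use that record only for a per-protocol sensitivity analysis, labelled as such. Define matching in advance, and make clear that following the assigned programme does not count as matching.

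The cost is about one sentence in each of the two sections and one extra question per assessment. The downside is that controls who take up exercise may dilute the estimate. In the illustration above, where exercising controls gain the full 3 units, analysing everyone gives 2.7 at 10% and 2.4 at 20%. That is the effect of offering the programme when outside exercise is unrestricted, and the sensitivity analysis can show how far contamination matters.
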